
#### Health economic outcomes

The Client Sociodemographic and Service Receipt Inventory (CSSRI-EU) [49] will be used to record service use. Costs from the perspective of the national economy are estimated by multiplying the units of services used by the identified costs of those units and the addition of indirect costs due to work incapacity. Based on the data in the CSSRI-EU, treatment pathways including delay until allocation as well as adherence to, discontinuation of and switches between services can be presented.

#### Implementation factors and outcomes

Comprehensive process evaluation will be based on routine data, surveys and qualitative studies to identify implementation processes as well as barriers and facilitators, especially with regard to the service user involvement, use of digital technologies in healthcare or interagency and interprofessional collaboration.

Therefore, a uniform routine documentation is implemented at the Regional Competence Centre and on the online platform. In addition, fidelity criteria will be assessed, and feedback data will be collected with the staff and service users via the online platform: During the intervention, routine data will be collected from service users, employees of the cooperation partners and the Regional Competence Centre. The routine data include, e.g., basic psychiatric recording data, treatment duration data in the Treatment Assistant and changes in wishes and goals of the service users during the treatment process. Also, the overall satisfaction with the Regional Competence Centre will be collected from the clients and the employees of the cooperation partners.

Subjective and collective views of service users, service providers and other stakeholders will be gathered through qualitative interviews and focus groups at the end of the implementation phase. A flexible guideline will be used, which covers the following main topics: (1) acceptance, content evaluation and practicality of the online and face-to-face services; (2) subjective assessment of the effects in terms of treatment retention and satisfaction; and (3) barriers and facilitators for active use of the coordination platform by patients, counsellors and treatment providers. The findings will help to further tailor the treatment coordination to the needs of users and to identify facilitators and barriers to sustainable implementation or scale-up.

### Participant timeline {13}

Participant recruitment will start on November 1, 2021, and is to be completed within 12 months. The individual participation period in the study will be 6 (intervention group) or 8 months (waitlist group). There will be four or five data collections at 2-month intervals (t0, t0 + 2 months [t1], t0 + 4 months [t2], t0 + 6 months [t3] and if applicable t0 + 8 months [t4]). The follow-up windows are defined as ± 4 weeks for the intended time point. The last data collection of the last study participant should be completed by July 1, 2023.

The following study schemes depict the time schedule of enrolment, interventions and assessments (Table 1).

**Table 1 Tab1:**
[figure not shown]
Time schedule

Process evaluation (routine data, additional polls and qualitative studies) are not depicted in the time schedule

^1^Standardized instrument

^2^If needed

^3^In the intervention group only

^4^In the waitlist group only

### Sample size {14}

Assuming a simplified statistical model (repeated measures design with within (time) × between (group) interaction, 2 groups, 4 time points) and a dropout rate of 40%, a sample size of 400 subjects allows the detection of an effect with a moderate effect size (Cohen’s *f* = 0.25 [50]) for the primary outcome (change in satisfaction (ZUF-8 Score) over 6 months) at a significance level of *p* < 0.05 with a power ≥ 0.90, as calculated by means of G*Power 3.1 [51].

### Recruitment {15}

The study will be introduced to PWUS via various channels (e.g. service providers, posters, flyers, press releases and online posts). Information is provided in personal conversations and/or via flyers and posters.

If a person is interested, an initial screening of the inclusion and exclusion criteria will take place, and if the substance user is eligible for participation, an appointment with a research associate will be scheduled. The initial screening can be made by telephone, online or in person.

## Assignment of interventions: allocation

### Sequence generation {16a}

Randomized assignment to the two study groups—intervention and waitlist—with a 1:1 allocation will be conducted using the ROM software [52] in order to avoid selection bias. A computer-generated randomization schedule with permuted blocks of random sizes will be used.

### Concealment mechanism {16b}

The independence of the group allocation from the data collection and analysis processes is guaranteed as randomization will be independently carried out by the Institute of Epidemiology and Medical Biometry at Ulm University.

All participants fulfilling the eligibility criteria and signing the informed consent form will be randomized. For this, research associates will schedule the baseline assessment (t0) and request randomization by e-mail from the Institute for Medical Biometry and Epidemiology, Ulm University, Germany. The randomization form includes the participant ID, approval of informed consent and eligibility. The requesting research associate will obtain a response by mail within one working day. Allocation disclosure will occur after the baseline assessment (t0) is completed.

### Implementation {16c}

The Institute for Medical Biometry and Epidemiology at Ulm University will generate the allocation sequence. The research associates will enrol participants, initiate randomization, collect baseline data, and assign the participants to the intervention group or the waitlist group. Thereafter, the research associate will provide access information for the online assessment to the participants of the intervention group and the study participants will complete the online assessment on their own. If required, the study participants will complete the online assessment at the premises of the Regional Competence Centre. Directly after the online assessment, a prompt appointment (best within 7 days) with the staff at the Regional Competence Centre is scheduled via the online platform. Participants in the waitlist group will receive access information for the online assessment only after completion of the third follow-up assessment (t3). This will be ensured by having two different code sets which grant access to the online platform. Only those codes provided to the intervention group are valid directly.

## Assignment of interventions: blinding

### Who will be blinded {17a}

Due to the nature of the intervention, blinding of the participants and service providers is not possible. Furthermore, it is not possible to blind the research associates, as they would be unblinded at the latest when collecting the data for the process evaluation. The same applies to all researchers involved in data monitoring and data management. Thus, only the researcher performing the main data analysis will be blinded until the main analysis has been completed.

### Procedure for unblinding if needed {17b}

Unblinding is not needed as participants, service providers and research associates will be unblinded to treatment allocation.

## Data collection and management

### Plans for assessment and collection of outcomes {18a}

Data collection will be carried out by the staff of Ulm University, who will be trained accordingly before the start of the study and will follow uniform standard operating procedures. Data collection will be carried out in face-to-face meetings at the Regional Competence Centre, the facilities of the Stuttgart addiction support system or somewhere else, or in online meetings, depending on the participants’ preferences and current contact restrictions due to the SARS-CoV-2 pandemic. At the beginning of each appointment, the evaluation staff will conduct a short admission interview to determine whether data collection is currently possible or whether there is a state of acute intoxication or acute crisis present.

As a standard, data is collected directly online via SoSci Survey (SoSci Survey GmbH, Munich). If electronic data collection is not possible, the data collection will be paper-based and transferred electronically within 1 week.

Study dropouts and serious adverse events will be documented on standardized forms.

The coordinator of the evaluation and research associates will check the quality of data collection during semiannual monitoring visits, focusing on the eligibility of included study participants as well as on the completeness and plausibility of the collected data. Furthermore, serious adverse events must be documented appropriately.

Routine data will be provided by participants via the online platform and collected by the Regional Competence Centre staff.

### Plans to promote participant retention and complete follow-up {18b}

In general, the research staff will try to fulfil the participants’ preferences regarding format (online or face-to-face), date and time when making the appointment for data collection.

The research staff will be in close contact with the study participants. At the end of the interviews, an appointment will be made for the next follow-up, which will take place after 2 months. Two weeks before this date, the participants will be reminded about the appointment. If necessary, an alternative appointment will be arranged. If the participants do not show up for the agreed appointment, they will be contacted again with the offer of an alternative appointment.

If it is not possible for the participant to be interviewed at the given time (e.g. due to a crisis or inpatient stay), the respective follow-up assessment may be omitted. Then, the research staff will attempt to arrange another appointment at the next possible time.

Participants will receive the following incentives: €10 at t0, €15 at t1, €20 at t2 and €25 at t3, and participants in the waitlist group receive €30 on t4. If applicable, they will be reimbursed for their expenses for travelling to the location of the interview.

If a participant declares his or her wish to drop out of the study, the time and the reasons for dropping out will be documented.

All deviations from the intervention protocol (including non-use and discontinuation) will be traceable using the data of the online platform and will be documented by the staff at the Regional Competence Centre.

### Data management {19}

Data will primarily be collected using the survey software SoSci Survey (SoSci Survey GmbH, Munich). When filling in the questionnaire electronically, the answer categories are pre-defined, and warnings appear if individual items have not been answered.

All collected study data will be regularly requested and stored on servers at the Department for Psychiatry and Psychotherapy II of Ulm University. Pseudonymized routine data will be provided as a .xlsx file by the intervention team at the end of the intervention phase and will be merged with study data by intervention identifier (ID). Data processing using software packages like SPSS, version 25and SAS version 9.4 will include electronic data checks for plausibility and completeness as well as the derivation of additional variables (such as scores) for analysis.

### Confidentiality {27}

The collection, storage and analysis of the study data will be carried out in compliance with the relevant data protection regulations. All personal data will be pseudonymized during the collection, by replacing the study participants’ personal identifying data with identifiers (study ID for study data and intervention ID for routine data). The index tables for the assignment of personal data and identifiers will be access-protected and stored separately from the data.

The research associates responsible for the data collection will be the only persons with access to the major index table with personal data, study identifiers and intervention identifiers.

Prior to enrolment in the study, the potential study participants will be informed orally and in writing about the study’s aims, nature, scope and implications as well as about the data protection regulations within the study by the research staff of Ulm University. The potential study participants will be given sufficient time to consider their participation and to ask questions. By signing the informed consent form, the potential study participant will agree to both, participating in the study and agreeing to the data protection regulations.

The study results will be published anonymously, making sure that identification of individual participants is not possible. The study data will only be transferred anonymously to third parties, including the sponsoring team and service providers of the addiction support system in Stuttgart.

The study data will be archived on servers at the Department for Psychiatry and Psychotherapy II of Ulm University.

### Plans for collection, laboratory evaluation and storage of biological specimens for genetic or molecular analysis in this trial/future use {33}

No biological specimens for genetic or molecular analysis will be collected in this trial.

## Statistical methods

### Statistical methods for primary and secondary outcomes {20a}

The analysis of the primary and secondary outcomes will follow the intention-to-treat (ITT) principle. Mixed models with fixed time effects and time × group interaction effects (fixed: time (4 or 2 time points), group (2 groups), time × group interaction; random: patient) will be applied. The time by group interaction will reflect the intervention effect.

The cost-effectiveness ratios from the perspectives of the national economy will be determined using the net benefit method.

Furthermore, for the waitlist group, the changes in the primary and secondary outcomes criteria during the waiting period (from t0 to t1) and after the assessment and treatment coordination (from t3 to t4) are compared using a paired *t*-test.

Implementation of sector-independent treatment coordination starting from an online assessment is evaluated mainly using descriptive methods (relative frequencies and measures of agreement). These methods are also used to show the extent to which treatment recommendations based on the online assessment and the interview at the Regional Competence Centre differ from each other and the extent to which actual treatment pathways match the recommendations. Fit is classified as less than adequate (treatment intensity lower than recommended), adequate (treatment intensity as recommended) and more than adequate (treatment intensity higher than recommended). The factors that influence fit and the extent to which fit affects the outcomes are also examined.

The statistical significance level will be set at *p* < 0.05. The statistical programmes IBM SPSS 25, STATA 15 and SAS 9.4 will be used for statistical analysis.

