### Outcomes {12}

#### Primary outcome

The primary outcome is the mid-term change in satisfaction with substance-related care over 6 months. With the increasing emphasis on patient engagement and continuous quality improvement in mental health care, evaluation has shifted to measuring the performance of a treatment programme in terms of treatment satisfaction [27]. Treatment satisfaction represents an important indicator of patient benefit [28]. The German short version of the Client Satisfaction Questionnaire (CSQ-8) [29], called the ZUF-8 Questionnaire [30], will be used every 2 months (t0, t1, t2, t3 and t4 if applicable).

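### The primary model estimates a baseline group difference that randomisation makes zero in expectation; a common t0 mean would gain precision at no cost

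*Protocol article*

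**What the plan says.** The section on statistical methods for primary and secondary outcomes {20a} specifies a mixed model with these terms: "fixed: time (4 or 2 time points), group (2 groups", followed by their interaction and a random patient effect. It then identifies the treatment effect: "The time by group interaction will reflect the intervention effect".

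Under Primary outcome, the ZUF-8 "will be used every 2 months (t0, t1, t2, t3 and t4 if applicable", and the target is a change: "The primary outcome is the mid-term change in satisfaction with substance-related care over 6 months". The t4 visit belongs to the waitlist group only, so the four time points shared by both arms are t0, t1, t2 and t3. The sample size section {14} uses the same structure: "repeated measures design with within (time) × between (group) interaction, 2 groups, 4 time points".

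Assignment to the groups "with a 1:1 allocation will be conducted using the ROM software" (Sequence generation {16a}). The Concealment section {16b} adds: "Allocation disclosure will occur after the baseline assessment (t0) is completed".

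The article mentions neither a baseline covariate nor a common baseline mean.

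**The concern.** Because t0 is one of the modelled time levels and group has its own main effect, the model estimates a separate t0 mean for each arm. Allocation is random and nobody is to be told the result before t0 is complete, so the expected difference at t0 is zero. The model spends information on estimating a quantity that the design already fixes.

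Two things follow. The estimate of the difference in change is less precise than the same data allow. And, for a given trial, a chance imbalance at t0 carries over into the estimate through regression to the mean. A trial that plans to lose 40% of its participants has reason to use all the information in a baseline score that it collects anyway.

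**Working it through.** **Inputs from the protocol.** 400 randomised 1:1, 40% dropout, Cohen's f = 0.25, α = 0.05, power ≥ 0.90, two groups, four time points (Sample size {14}); model terms from {20a}; no imputation in the main analysis ({20c}).

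**Assumed, because the protocol gives no value.** The correlation ρ between ZUF-8 scores of the same patient, taken as 0.3 to 0.7 with higher values shown. Equal variances and equal correlations across visits, which is what a random patient intercept implies.

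**Step 1: the plan's own power.** Completers: 400 × 0.6 = 240. Noncentrality with Cohen's definition of f: λ = f² × N = 0.0625 × 240 = 15. With 3 numerator degrees of freedom, power is 0.915 (714 denominator df) or 0.912 (236 denominator df). The other G*Power conventions tried give more than 0.999. The stated figure holds.

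**Step 2: complete data.** With n per arm and outcome variance σ², the variance of the t0-to-t3 group contrast is:
- free baseline (model as written): 2σ²(1−ρ) × 2/n, exactly that of the difference in raw change scores;
- common baseline mean: σ²(1−ρ²) × 2/n.

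The ratio of the second to the first is (1+ρ)/2, so the share of precision lost is 1 − (1+ρ)/2 = (1−ρ)/2.

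**Step 3: planned dropout.** For t0 and t3 alone, with everyone seen at t0 and 60% at t3, the likelihood estimate has a relative efficiency of (1+ρ)/[(1+ρ) + 0.6(1−ρ)]:
- ρ = 0.3: 1.3/(1.3 + 0.42) = 0.76
- ρ = 0.5: 1.5/(1.5 + 0.30) = 0.83
- ρ = 0.7: 1.7/(1.7 + 0.18) = 0.90

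A generalised least squares calculation with all four visits, and the 40% dropout spread evenly and monotonely over t1 to t3, agrees:

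| ρ (assumed) | Variance loss, complete data | Variance loss, 40% dropout | SE loss, complete data | SE loss, 40% dropout |
|---|---|---|---|---|
| 0.3 | 35% | 25% | 19% | 13% |
| 0.5 | 25% | 17% | 13% | 9% |
| 0.7 | 15% | 10% | 8% | 5% |
| 0.8 | 10% | 7% | 5% | 3% |
| 0.9 | 5% | 3% | 2.5% | 2% |

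The loss is smaller under dropout because participants seen only early still inform the model. For the same reason the estimate is then no longer exactly the raw change-score difference.

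**Step 4: the joint test.** If the effect is read from the 3-df interaction test and not from t3 alone, the loss depends on the shape of the effect. For ρ = 0.3 to 0.7 with complete data it is about 53% to 22% for an effect constant over t1 to t3, and 40% to 15% for one growing linearly.

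**Step 5: chance imbalance.** With 200 per arm, the baseline difference has a standard deviation of √(2/200) = 0.1 SD units. Given such an imbalance, the complete-data change-score estimate shifts by (1−ρ) times it, in the opposite direction: 0.05 SD at ρ = 0.5.

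**The case against.** The strongest reply is that nothing here is wrong. The model is standard and unbiased over randomisation, it suits an outcome defined as a change, it matches the model used for sizing, and it meets its power target. All of that stands. It does not remove the point: the common-baseline model estimates the same between-arm difference in change from t0, only more precisely.

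A second reply is that baseline handling belongs in the statistical analysis plan, which is not shown. That plan may refine it. But the article writes out the fixed and random terms of the primary model, so this is a stated choice and not an open detail.

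A third reply is technical. The formula (1−ρ)/2 assumes equal variances. In general, with complete data, the change-score variance exceeds the adjusted variance by (σ₀ − ρσ₃)², which vanishes when ρσ₃/σ₀ = 1, for example at ρ = 0.8 and σ₃/σ₀ = 1.25. The loss can therefore be zero, though the common-baseline model is never the less precise one. This stands as a limit on the size.

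A reader might go further and infer two things that the documents do not support:
- That the 240 completers could be made to work like 320. At ρ = 0.5 with complete data, 240/0.75 = 320. But this treats the analysis as completers-only, whereas the planned model uses all available visits. Under the planned dropout the gain at ρ = 0.5 is worth about 20% more participants (1/0.83), and ρ itself is assumed.
- That the trial is underpowered. For a t3 difference of 0.36 SD at ρ = 0.5 with 120 per arm, power is 0.796 with change scores and 0.896 with adjustment. The 0.36 SD appears nowhere in the protocol; it is roughly the difference that the adjusted analysis detects with 90% power, so the comparison is circular. The trial was sized on f = 0.25 for the interaction.

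**Conclusion.** The point holds as an efficiency recommendation. The primary model leaves free a baseline difference that the design makes zero in expectation, and pays for it in precision. It is not a source of bias and does not undermine the stated power.

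On the t0-to-t3 contrast the loss is (1−ρ)/2 in variance terms with complete data and equal variances. With ρ assumed between 0.3 and 0.7, that is 35% to 15% with complete data and about 25% to 10% under 40% dropout spread evenly over follow-up. With complete data it falls to 10% and 5% at ρ = 0.8 and 0.9. The direction is secure wherever the disclosure rule in {16b} is kept; the size rests on a correlation that the protocol does not report.

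The gain is still worth taking. The reproduced power of 0.91 leaves little margin if the effect is smaller or dropout higher than assumed, and the sample size section covers only the primary outcome.

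**What to change.** Before any unblinded analysis, restate the model: keep t0 in the outcome vector, give both arms a common t0 mean by removing the group effect at t0, and let group × t1, group × t2 and group × t3 carry the intervention effect. Treat each secondary outcome in the same way, with its own baseline and its own follow-up visits: t1 and t3, or t3 alone for outcomes measured twice.

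Using t0 as a covariate with the later visits as outcomes is equivalent only when data are complete, so with the planned dropout the constrained model is the better choice.

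The cost is one sentence in the analysis plan and a small change in the model code. No extra data or participants are needed, and the quantity estimated stays the between-arm difference in change from baseline.

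### With patient as the only random term, the primary mixed model assumes equal correlation between all visits; if correlation fades with time, the standard error of the 6-month effect is too small

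*Protocol article*

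**What the plan says.** The section Statistical methods for primary and secondary outcomes {20a} of the protocol article lists the model terms: "fixed: time (4 or 2 time points), group (2 groups), time × group interaction; random: patient". It mentions no random slope, residual covariance structure or robust standard error. On inference it says "The time by group interaction will reflect the intervention effect", without saying whether this means the joint interaction over all visits or a single contrast.

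The Primary outcome section states: "The primary outcome is the mid-term change in satisfaction with substance-related care over 6 months". The ZUF-8 "will be used every 2 months (t0, t1, t2, t3 and t4 if applicable"), and t4 applies to the waitlist group only. The randomised comparison therefore rests on four visits, t0 to t3, spaced 2 months apart (Participant timeline {13}: "There will be four or five data collections at 2-month intervals").

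The Sample size {14} section uses a "repeated measures design with within (time) × between (group) interaction, 2 groups, 4 time points", with Cohen's f = 0.25, 40% dropout and power of at least 0.90. It gives no correlation between visits and no sphericity correction.

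**The concern.** A random patient intercept with independent residuals gives compound symmetry. The model then treats t0 and t3, 6 months apart, as being as strongly correlated as t0 and t1, 2 months apart. If a participant's satisfaction scores become less alike as the interval grows, the model applies an average correlation to the pair with the lowest one. The variance of the t0-t3 change is then underestimated, and the error favours a positive result.

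The primary outcome is defined over exactly that longest interval. The planned sensitivity analysis would not show the problem, because the section on non-adherence and missing data {20c} applies the same model to each imputed dataset. The substance-group model in {20b} extends it as well. The main analysis also relies on the mixed model, without imputation, to deal with up to 40% dropout, so the within-patient covariance matters for more than the standard error.

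**Working it through.** **Inputs from the article.** Four visits at 2-month spacing; two arms, 1:1; 400 randomised; 40% dropout, so 400 × 0.6 = 240 analysed; two-sided 5% level. The correlations between visits are not given. Those below are assumed, with equal variances at all visits.

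**The plan's own figure.** For the interaction test with 240 analysed, df1 = 3 and df2 = 3 × 238 = 714. The most conservative noncentrality tried is f² × N = 0.0625 × 240 = 15, which gives power of about 0.92. The other conventions tried give more than 0.999. The stated power of at least 0.90 is reproduced (under sphericity), and this point does not overturn it.

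**Formula for the t0-t3 contrast.** With four complete visits, the random-intercept model estimates the residual variance as σ²(1 − mean ρ), where mean ρ averages the six pairwise correlations. The true variance of the change is proportional to 1 − ρ(t0,t3). Hence

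- SE ratio (model/true) = √[(1 − mean ρ) / (1 − ρ(t0,t3))]
- actual type I error = 2 × [1 − Φ(1.96 × ratio)]

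**Worked case, AR(1) with adjacent correlation 0.7.** The correlations at 2, 4 and 6 months are 0.7, 0.49 and 0.343. Mean ρ = (3 × 0.7 + 2 × 0.49 + 0.343) / 6 = 0.5705. The ratio is √(0.4295 / 0.657) = 0.809. Then 1.96 × 0.809 = 1.585, and the type I error is 11.3%.

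**Joint 3-df test.** Its size is approximated with Box's ε: the 5% critical value of F(3, 714) is referred to F(3ε, 714ε). In the worked case ε = 0.769 and the size is 6.57%.

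| Assumed correlations at 2/4/6 months | Mean ρ | SE ratio, t0-t3 | Type I error, t0-t3 | Type I error, joint test |
|---|---|---|---|---|
| constant 0.5 | 0.500 | 1.000 | 5.0% | 5.00% |
| 0.6/0.55/0.5 | 0.567 | 0.931 | 6.8% | 5.12% |
| AR(1) 0.3 | 0.185 | 0.915 | 7.3% | 5.37% |
| 0.6/0.5/0.4 | 0.533 | 0.882 | 8.4% | 5.41% |
| AR(1) 0.5 | 0.354 | 0.859 | 9.2% | 5.91% |
| 0.7/0.6/0.5 | 0.633 | 0.856 | 9.3% | 5.65% |
| AR(1) 0.7 | 0.570 | 0.809 | 11.3% | 6.57% |
| AR(1) 0.8 | 0.699 | 0.786 | 12.4% | 6.92% |
| AR(1) 0.9 | 0.842 | 0.765 | 13.4% | 7.28% |

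**Simulation check.** A REML random-intercept fit was run 1,500 times per case, first with 120 complete participants per arm and then with 200 per arm and 40% random monotone dropout by t3. The type I error of the t0-t3 contrast (complete, then dropout) was:

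- constant 0.5: 4.4%, 4.6%
- AR(1) 0.5: 9.4%, 9.4%
- 0.7/0.6/0.5: 9.5%, 9.1%
- AR(1) 0.7: 11.9%, 11.3%

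The Monte Carlo standard error is about √(0.05 × 0.95 / 1500) = 0.6 percentage points at 5%, and about 0.8 at 11%. The simulation agrees with the formula, and dropout at random changes little.

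**Secondary outcomes.** For those measured at t0, t1 and t3, if all three visits enter the model, AR(1) 0.7 gives mean ρ = (0.7 + 0.49 + 0.343) / 3 = 0.511, a ratio of √(0.489 / 0.657) = 0.863 and a type I error of 9.1%. Outcomes measured only at t0 and t3 have a single correlation, so compound symmetry places no restriction on it and there is no inflation.

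**The case against.** Three objections carry weight.

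1. **The residual covariance is not stated.** Random effects and residual covariance are separate parts of a mixed model. A random patient term is compatible with serially correlated residuals, which would remove or reduce the problem, and such detail is commonly left to the SAP. This stands as a limit: equal correlation follows only if the residuals are independent. It does not dispose of the point, because the article lists the random part explicitly, and an analyst following that list with software defaults would fit a plain random intercept.

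2. **The larger error rates belong to a test that the article does not name.** Both {20a} and the sample-size section point literally to the joint time × group interaction, where the inflation is only about 5% to 7%. This stands. The t0-t3 contrast remains relevant because it best fits the outcome definition.

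3. **The size rests on assumed correlations.** This also stands. A pure AR(1) pattern has no stable participant component and is a steep decay. The gentlest fading pattern tried gives 6.8% for the contrast, and a constant correlation gives 5.0%.

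A reader might therefore infer that the standard errors of this trial are wrong and that its false-positive rate lies well above 5%. The article does not support that. It requires independent residuals, fading correlation and the t0-t3 contrast as the test, and the article states none of the three.

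**Conclusion.** The point holds in conditional form. Fitted as written with independent residuals, the model ties the 6-month correlation to the average over all visit pairs. If ZUF-8 correlation fades with time, the joint interaction test has a type I error of about 5% to 7%. The standard error of the t0-t3 contrast is about 7% to 24% too small, with a type I error of about 7% to 13%. With constant correlation there is no inflation. These ranges assume equal variances across visits and, in the simulations, dropout at random.

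The article contains no contradiction or arithmetic error on this point, and its power statement survives. The appropriate grade is should-fix rather than must-fix: the possible error concerns the primary effect and is cheap to remove before analysis.

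**What to change.** For outcomes with three or more time points in the randomised comparison:

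- Replace the lone random patient term with an unstructured within-patient covariance, 4×4 for the primary outcome, and use Kenward-Roger degrees of freedom.
- Prespecify a fallback if it does not converge: heterogeneous Toeplitz, or a random intercept with sandwich standard errors.
- Name the group difference in change from t0 to t3 as the primary test, so that it matches the primary outcome definition.
- Use the same covariance in the analysis of the imputed datasets.

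An unstructured covariance targets an SE ratio of 1.0 and a 5% error rate under every pattern in the table. The cost is a line of SAP text and code in SAS 9.4, which the article already lists. The 4×4 matrix has 4 × 5 / 2 = 10 covariance parameters against 2 for the random intercept, a negligible loss with 400 participants. The remaining downside is that the fallback may be needed. If correlation is in fact constant, almost nothing is lost.
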